#### Analyses of patient-related outcomes

The patient-related outcomes, specifically patient engagement (H1, H3) and perceived quality of care (H2, H4), will primarily be analyzed with two separate mixed-design (split-plot) analyses of variance (ANOVA), with group as the between-subjects factor (2 groups: standard care, standard care with robot interactions) and time as the within-subjects factor (2 levels: T1 and T2; see Figure 1). Significant results will be followed up with *post hoc* tests using the correction to adjust for multiple testing. All results will be accompanied by effect sizes.

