### Study design

The proposed study employs a between-within interaction design with multiple iterations. Patients and employees participating in the study will be recruited in a University Clinical Centre Maribor, Slovenia. The study will be carried out in 1-week intervals, followed by a 1-week washout period between each iteration. Overall, the study will be conducted over 2 years or less if the desired sample size is reached sooner.

Patients admitted to vascular and thoracic surgery wards for an elective (non-emergency) procedure will be screened for eligibility regarding the inclusion and exclusion criteria. Eligible participants will then be informed about the study characteristics and asked to fill out an informed consent form. Those who will consent to participate in the study will participate for 3–5 days. Depending on the week (see Figure 1), participants will be allocated to the standard care group (i.e., a control group that will not interact with a socially assistive robot) or standard care group with additional robot interactions. Participants from both groups will first be informed about the study and fill out the baseline questionnaires (demographic data, engagement, and perceived quality of care). Similarly, participants from both groups will be subjected to standard nursing education and general/respiratory physiotherapy delivered by nursing and physiotherapy staff. However, the patients allocated to the standard care group with additional robot interactions will additionally be subjected to nursing education and general/respiratory physiotherapy delivered by a socially assistive robot. Moreover, they will be able to call the robot for additional assistance (not related to nursing education and physiotherapy) during the whole study period. At the end of their participation, patients from both groups will be asked to fill out the questionnaires (engagement, perceived quality of care) for the second time. Patients from both groups will also be asked to rate the education and physiotherapy they received during the study period. Moreover, patients that will interact with a socially assistive robot, will also fill out the User Experience Questionnaire (30) at the end their participation.

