**FIGURE 1 F1:**
[figure not shown]
Study design: patients.

The study will be conducted in several 1-week iterations with a washout period between them (to provide enough time for new patients to be admitted). Specifically, patients will receive standard care in week 1, followed by a washout period in week 2. Patients in week 3 will then receive standard care together with robot interactions, followed by a washout period in week 4. In week 5, patients will again receive standard care. The study procedure (for patients) is outlined in Figure 1. It is worth noting that all additional variables (e.g., number of interactions with a robot) will be collected continuously during each relevant iteration. Additionally, the instructions of all self-report questionnaires will be adapted to reflect the chosen time periods and tasks. Throughout the study, patients will be observed for signs of high distress and excluded from the study if needed.

In terms of intervention content, the nursing education will contain critical information on wound care, home care considerations, and daily care explanations. On the other hand, general and respiratory physiotherapy will consist of selected instructions and exercises that can be delivered both by a human and a robot. The AI-delivered nursing education and physiotherapy instructions will employ elements of gamification.

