The proposed study is not without limitations. First, while our study will offer important insight into the effectiveness of interactive digital assistance, a randomized controlled trial with a larger sample size may be needed to further determine the effects of such intervention. Second, even though all surgery patients conforming with the inclusion criteria will be invited to participate in the study, it is plausible that only patients with more favorable attitudes toward technology will agree to participate in the study. This might lead to a sample that is generally younger and more educated (43, 44), possibly biasing the results on the effectiveness of social robot-delivered education and physiotherapy. Third, due to the specific characteristics of vascular and thoracic surgery patients (e.g., length of hospitalization), their exposure to the social robot will be somewhat short. Hence, the study will primarily focus on initial reactions to the socially assistive robot, whereas the trajectories of what happens over a more extended period (i.e., continued use), which can differ from initial reactions (45), will have to be explored in future studies. Lastly, in the present study, the social robot will be limited to a few specific services, physical locations, and one hospital, making it difficult to provide general and final conclusions on the effectiveness of social robots in hospitals.

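### The patient comparison for H3 and H4 is not randomised, yet its primary model adjusts for no baseline characteristic, so an arm imbalance in anything related to change biases the group-by-time interaction

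*Protocol article*

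**What the plan says.** All references are to the protocol article.

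- **Allocation (Study design).** "Depending on the week (see Figure 1), participants will be allocated to the standard care group" or to standard care plus robot. The order is a fixed alternation: "patients will receive standard care in week 1, followed by a washout period in week 2", then a robot week, a further washout week, and standard care again.
- **Baseline data (Study design).** Both groups "fill out the baseline questionnaires (demographic data, engagement, and perceived quality of care"). The Measures section adds only that basic demographic questions are asked and does not list them.
- **Hypotheses (Introduction).** H3 and H4 predict a larger improvement in the robot group than under standard care. The test is therefore the group-by-time interaction.
- **Model (Analyses of patient-related outcomes).** The outcomes "will primarily be analyzed with two separate mixed-design (split-plot) analyses of variance (ANOVA"). Only two factors are named, the model being specified "with group as the between-subjects factor (2 groups: standard care, standard care with robot interactions) and time as the within-subjects factor". The Data analysis section describes no covariate and no adjusted model.
- **Limitations (Discussion).** The article concedes that "a randomized controlled trial with a larger sample size may be needed to further determine the effects of such intervention". It also says that patients with favourable attitudes to technology may be the ones who consent: "This might lead to a sample that is generally younger and more educated (43, 44), possibly biasing the results on the effectiveness" of the intervention.

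**The concern.** H3 and H4 are the only controlled patient comparisons; H1 and H2 compare robot patients with their own starting values. In a randomised trial, a model with group and time alone would be valid, because baseline differences would be due to chance and the test would allow for them. Here, assignment by week gives no such guarantee. The alternation is fixed, so the arm is foreseeable when consent is sought, and the patients who enter in robot weeks may differ from those who enter in control weeks.

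Subtracting T1 removes any characteristic that shifts T1 and T2 equally. It does not remove one that affects how much a patient changes over 3–5 days. If such a characteristic is unbalanced between arms, part of the difference in change is attributed to the robot, or a real effect is masked. The article collects data that could reduce this problem and then leaves them out of the model. Because the model is stated outright as primary, this is an analysis choice that the article fixes, not a detail left to a fuller plan.

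**Working it through.** **Inputs from the article (Participants and recruitment):** 2 groups, 2 measurements, f = 0.15, α = 0.05, power 0.80, about 90 patients.

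**Assumed, because not stated:** T1–T2 correlation ρ = 0.5; equal arms of 45; the size of the arm imbalance; the slope of change on the covariate.

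**1. Reproduce the planned sample size.** Noncentral F with λ = f²·N·m/(1 − ρ) = 0.0225 × 90 × 2 / 0.5 = 8.1, on 1 and 88 df. Power is 0.804, and 90 is the smallest even N that reaches 0.80. The article's figure reproduces at ρ = 0.5. It would be 126 at ρ = 0.3 and 56 at ρ = 0.7.

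**2. Convert to a difference in change.** In a 2 × 2 layout, the difference between arms in mean change is 4f = 4 × 0.15 = 0.60 SD. The SD of change is √(2(1 − ρ)) = 1 SD. The standard error of the arm difference is √(2/45) = 0.211 SD. Check: 0.60/0.211 = 2.85 = √8.1.

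**3. Bias from an unbalanced covariate.** Bias = imbalance × slope, both per SD of the covariate. With no true robot effect, the type I error is the two-sided rejection rate of a noncentral t on 88 df with noncentrality bias/0.211.

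| Imbalance (SD) | Slope (SD of change per SD) | Bias (SD) | Share of 0.60 | Type I error |
|---|---|---|---|---|
| 0.3 | 0.2 | 0.06 | 10% | 5.9% |
| 0.3 | 0.3 | 0.09 | 15% | 7.1% |
| 0.5 | 0.2 | 0.10 | 17% | 7.6% |
| 0.5 | 0.3 | 0.15 | 25% | 10.8% |

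Over a wider range (imbalance 0.2–0.5, slope 0.1–0.4), the bias is 0.02–0.20 SD and the type I error 5.1–15.5%.

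**4. Simulation check (4,000 runs, N = 90, imbalance 0.5 SD).**
- Covariate affects level only (0.4 SD per SD at both T1 and T2): bias 0.006 SD, rejection 5.4%. This is no bias beyond simulation error.
- Covariate affects change (slope 0.3): bias 0.146 SD, rejection 10.9%. With the covariate in the model: bias −0.002 SD, rejection 5.1%.

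**5. Power after adjustment, under the same imbalance.** One covariate with slope s removes a share s² of the variance of change. An imbalance d inflates the variance of the group effect by 1 + d²/4. So SE = 0.211 × √[(1 − s²)(1 + d²/4)], on 87 df:

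| d | s | 1 + d²/4 | 1 − s² | Power |
|---|---|---|---|---|
| 0.3 | 0.2 | 1.0225 | 0.96 | 0.811 |
| 0.3 | 0.3 | 1.0225 | 0.91 | 0.831 |
| 0.5 | 0.2 | 1.0625 | 0.96 | 0.796 |
| 0.5 | 0.3 | 1.0625 | 0.91 | 0.817 |

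The unadjusted figure is 0.804. Power therefore stays close to plan and can fall slightly.

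**The case against.** **The interaction already controls for baseline.** This stands for stable level differences, as step 4 of the working shows. Bias needs both an arm imbalance and a covariate effect on change over a short stay, and the documents give a size for neither. That makes the amount uncertain. It does not make the unadjusted model safe, since nothing in the allocation keeps the arms comparable.

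**The Discussion does not predict an imbalance between arms.** A reader might infer from "This might lead to a sample that is generally younger and more educated (43, 44), possibly biasing the results" that the authors expect the arms to differ in age and education. The text does not say so: it describes who consents to the study as a whole. Adjusting within a narrower sample would not cure that limitation. A reader might also infer that patients in robot weeks consent more selectively because they are asked to accept a robot. Study design describes one sequence of information and consent for both groups and does not say that the information differs by week. Differential consent is possible but undocumented. The point does not depend on it, because it follows from allocation without randomisation.

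**Covariate data may not suffice.** Education is not named among the demographic items, so its availability is an assumption. Ward is known from recruitment.

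**The article says the outcomes are primarily analysed this way, so adjusted models may appear in a fuller plan.** Supporting analyses are not excluded. But the analysis that decides H3 and H4 is stated, and it is unadjusted. The concession that a randomised trial may be needed acknowledges the weakness without reducing it.

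**Conclusion.** The point holds in a limited form. The primary model for a comparison allocated by calendar week uses group and time only, and so leaves the group-by-time interaction open to confounding by baseline characteristics related to change. It would be wrong to say that every arm difference in age or education passes into the robot effect; only the part related to change does.

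The size is illustrative. It rests on N = 90 in equal arms, a T1–T2 correlation of 0.5, an imbalance of 0.3–0.5 SD and a slope of 0.2–0.3, of which only N comes from the article. On those values the bias is 0.06–0.15 SD, or 10–25% of the planned 0.60 SD, and the nominal 5% test rejects about 6–11% of the time when the robot has no effect. Zero bias is also possible, if the arms happen to be balanced or the covariates are unrelated to change.

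The case rests on bias alone. A reader might expect adjustment to buy precision as well, but under the imbalance that makes it necessary, power is about 0.80–0.83 against 0.80, so no gain can be claimed.

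**What to change.** In Analyses of patient-related outcomes, state before the data are examined that:

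1. The H3 and H4 models adjust for named baseline covariates already available: age (continuous), sex, ward (vascular or thoracic), and education if it is among the demographic items. If the mixed ANOVA is kept, each covariate must interact with time, because a covariate main effect alone leaves the group-by-time interaction unadjusted.
2. The adjusted group effect on change is the main result, with the unadjusted estimate reported alongside.
3. These variables are tabulated by arm.

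This takes a sentence or two and a few degrees of freedom, with no new data collection for variables already recorded. Naming the covariates now also prevents their being chosen after the results are seen. Adjustment does not deal with unmeasured confounders or with calendar effects, which come with allocation by week and should remain among the stated limitations.

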### Participants and recruitment

The proposed study intends to recruit two distinct samples: patients and staff. The patient sample will be composed of patients admitted to vascular surgery and thoracic surgery wards for an elective (non-emergency) procedure. Beyond the type of disease for patients, patients need to be aged 18 years or above and willing to participate in the study. On the other hand, exclusion criteria include emergency patients, patients already enrolled in other studies, patients with dementia, special needs or appointed guardians, and patients allocated to an intensive step-down unit and/or regimen.

The staff sample will be composed of nursing and physiotherapy staff working on either the vascular surgery or the thoracic surgery ward. Again, only employees aged 18 years or above, who have signed a consent form, will be invited to participate in the study.

To minimize background noise while ensuring that all patients also receive standard care, the study will employ a between-within interaction design, whereby patients will be allocated either to the (1) standard care group or (2) standard care with additional robot interactions. We performed the sample size calculation in the G*Power software (31), choosing the ANOVA repeated measures with within-between interaction (2 groups, 2 measurements) as the statistical test, entering a small-to-medium effect size (*f* = 0.15), and choosing a conventional significance threshold and power (α = 0.05, 1-β = 0.80). Such calculations suggest that approximately 90 patients need to be recruited overall.

The nursing and physiotherapeutic staff will be studied with a simpler within-subjects design, whereby all consenting employees will fill out the questionnaires after a period of standard care and after the use of a socially assistive robot. As such, we performed the sample size calculation in the G*Power software, choosing the Paired-samples *t*-test as the statistical test, entering a medium effect size (*d* = 0.50), and choosing a conventional significance threshold and power (α = 0.05, 1-β = 0.80). Such calculations suggest that at least 34 nursing and physiotherapeutic employees must be recruited overall.

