### Measures

Testing the primary hypotheses will require the measurement of several outcomes, namely patient engagement and perceived quality of medical care as well as self-efficacy and workload of staff. All questionnaires will be administered in Slovene. For questionnaires that have not yet been translated to this language and validated, we will use a standard procedure that involves translation and back-translation by qualified translators (32). Additionally, basic psychometric properties of the translated scales, such as internal reliability, will be tested prior to the main analyses.

Patient engagement will be measured with the Patient Health Engagement scale [PHE (33)], which consists of nine ordinal items. In the proposed study, we will convert the response format into a 5-point agreement scale ranging from “*completely disagree*” to “*completely agree*.” An example item is: “*Despite my illness, I know how to manage my life*.” The scale generally exhibits high correlations with concurrent measures, such as the Patient Activation Measure (34), and demonstrates solid reliability [test-retest and internal reliability (33)].

To measure the perceived quality of medical care, we will use the Perceived Quality of Medical Care scale [PQMC (35)]. The scale consists of six items (e.g., “*Medical care I have received was unsatisfactory/satisfactory*”), answered using a 7-point semantic differential scale. The scale is unidimensional and has previously exhibited excellent internal reliability [Cronbach α = 0.94 (36)].

The New General Self-Efficacy Scale [NGSE (37)] will be used to measure the extent to which employees believe they can achieve their goals. The NGSE is composed of eight items (e.g., “*I will be able to achieve most of the goals that I set for myself*”), which are answered on a 5-point agreement scale from “*strongly disagree*” to “*strongly agree*.” The overall score is then calculated by taking the average of all items. The scale is widely used in articles studying the adult population and generally exhibits high validity and reliability [Cronbach α = 0.86 (37)].

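### H3 and H4 are tested on the change from baseline; adjusting T2 for T1 uses the same data with more power unless the T1–T2 correlation is high

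*Protocol article*

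**What the plan says.** The section on analyses of patient-related outcomes makes two mixed-design ANOVAs the primary analysis, one for engagement (PHE) and one for perceived quality of care (PQMC). Group is the between-subjects factor, and "time as the within-subjects factor (2 levels: T1 and T2; see Figure 1" describes the other factor. T1 is therefore one level of the outcome and not a covariate. The Introduction words H3 and H4 as larger improvement in the robot group, and H1 and H2 as a rise from the start of the study within the robot group.

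The sample size section matches this test: "choosing the ANOVA repeated measures with within-between interaction (2 groups, 2 measurements) as the statistical test". Its inputs are an f of 0.15, a 5% significance level and 80% power. It concludes: "Such calculations suggest that approximately 90 patients need to be recruited overall". No T1–T2 correlation is given.

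On timing, the Study design section has both groups first "fill out the baseline questionnaires (demographic data, engagement, and perceived quality of care"); the study education, physiotherapy and, in the robot weeks, robot contact come afterwards. The example PQMC item in Measures reads "Medical care I have received was unsatisfactory/satisfactory". The Study design section adds that "the instructions of all self-report questionnaires will be adapted to reflect the chosen time periods and tasks". Allocation depends on the calendar week.

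**The concern.** A change score fixes the coefficient of baseline at 1, whatever the data show. When the T1–T2 correlation is moderate, that over-corrects and adds baseline noise to the comparison. ANCOVA estimates the coefficient from the same two measurements. What is at stake is power for H3 and H4 in a study of about 90 patients that has none to spare at the correlation its own sample size implies.

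PQMC gives a particular reason to look at this. Its item asks about care already received, and T1 is completed before the care under study. T1 and T2 therefore at least partly rate different care. That leaves the correlation uncertain and makes the T2–T1 difference harder to read as improvement in one quantity.

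**Working it through.** **Inputs.** From the sample size section: f = 0.15, α = 0.05, power 0.80, N about 90, 2 groups, 2 measurements. Assumed, because not stated: equal arms (45 each), equal SD at T1 and T2, T1–T2 correlation ρ over a range, no baseline difference in expectation, no dropout, no correlation among patients of the same week.

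**Step 1: reproduce N.** For the within-between interaction the noncentrality is λ = f²·N·2/(1−ρ), with 1 and N−2 degrees of freedom. At ρ = 0.5 and N = 90, λ = 0.0225 × 90 × 2/0.5 = 8.1 and power is 0.804; N = 89 gives 0.799. So 90 is exactly right at ρ = 0.5. At ρ = 0, 0.3 and 0.7 the same inputs need 178, 126 and 56 patients. The stated figure thus implies ρ of about 0.5.

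**Step 2: put f on the outcome scale.** The t-test on T2–T1 has λ = d²·(N/4)/[2(1−ρ)], where d is the between-group difference in change, in SDs of a single measurement. Equating this with step 1 gives d² = 16f², so d = 4 × 0.15 = 0.60. Check at ρ = 0.5: 0.36 × 22.5/1 = 8.1.

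**Step 3: compare three analyses for d = 0.60, N = 90.** Here d²·N/4 = 8.1, and each analysis divides it by its own variance:
- change: 2(1−ρ), 88 df
- ANCOVA: 1−ρ² = (1−ρ)(1+ρ), 87 df
- T2 alone: 1, 88 df

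The variance ratio of ANCOVA to change is (1−ρ)(1+ρ)/[2(1−ρ)] = (1+ρ)/2.

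| ρ | (1+ρ)/2 | λ change | λ ANCOVA | Power change | Power ANCOVA | Power T2 alone |
|---|---|---|---|---|---|---|
| 0.2 | 0.60 | 5.06 | 8.44 | 0.61 | 0.82 | 0.80 |
| 0.3 | 0.65 | 5.79 | 8.90 | 0.66 | 0.84 | 0.80 |
| 0.5 | 0.75 | 8.10 | 10.80 | 0.80 | 0.90 | 0.80 |
| 0.7 | 0.85 | 13.50 | 15.88 | 0.95 | 0.98 | 0.80 |
| 0.8 | 0.90 | 20.25 | 22.50 | 0.994 | 0.997 | 0.80 |

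Simulation with 20,000 runs per value agrees: 0.66 against 0.84 at ρ = 0.3, 0.80 against 0.90 at 0.5, 0.95 against 0.98 at 0.7.

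**Step 4: crossover.** Change has a larger variance than T2 alone when 2(1−ρ) > 1, that is when ρ < 0.5. The correlation implied by N = 90 is exactly this break-even point: there the planned test gains nothing from having measured baseline.

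**Step 5: in patients.** For 80% power, change against ANCOVA needs 126 against 82 at ρ = 0.3, 90 against 68 at 0.5, and 56 against 48 at 0.7.

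**The case against.** **Hypothesis, sizing and test agree with each other.** H3 and H4 speak of improvement, the sample size is for the interaction, and the interaction is tested. This stands: nothing is contradicted, and a reader who infers that 90 is miscalculated would be mistaken. The point is lost efficiency.

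**The gain depends on an unknown correlation.** This also stands; at 0.8 or above there is little to gain. It is tempting to say that the PQMC correlation is likely to be low, but the article gives no data on it, and for PHE it gives no reason to expect a low value. The low-ρ rows are a range, not a forecast.

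**Groups are formed by week, not randomised.** This is the strongest objection. If the groups differ at T1, the two estimates differ by (1−ρ) times the baseline difference. For an assumed 0.3 SD difference at ρ = 0.3 that is 0.7 × 0.3 = 0.21 SD, about a third of 0.60, and which estimate is biased depends on why the groups differ. It does not overturn the point, because the week rule does not depend on a patient's T1 score. But consent or case mix may differ between weeks, so the change analysis should be kept alongside.

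**PQMC at T1 may still rate real care.** Patients may already have received other care around admission, and the questionnaire instructions are to be adapted to the period. The exact T1 wording is a detail an article may leave to the full protocol. A reader might infer that H2 has no meaning or that improvement must be dropped from H2 and H4. The article supports less: the two ratings refer at least partly to different care, so the change calls for cautious interpretation.

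**Conclusion.** The concern holds as a matter of efficiency. At the correlation implied by the article's own sample size (0.5), ANCOVA raises power for a 0.60 SD difference from 0.80 to 0.90. The gain is larger below that correlation, about 2 points at 0.7, and negligible from 0.8 upwards. In noncentrality ANCOVA is never behind, and it costs one degree of freedom. These figures rest on equal arms, equal SDs, no expected baseline difference and no within-week correlation.

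The possible mismatch between T1 and T2 makes the choice of test potentially most important for PQMC, but the documents do not establish how low its correlation is. Nor do they support treating ANCOVA as protection against non-randomised allocation.

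**What to change.** - Make ANCOVA the primary test of H3 and H4: T2 score on group, adjusted for the T1 score of the same scale. State this before outcomes are compared by group.
- Report T1 scores by group, and keep the group × time result as a sensitivity analysis. If the two disagree, discuss the baseline difference openly.
- Keep the within-group T1–T2 comparison for H1 and H2, which ANCOVA does not test. For PQMC, say that T1 precedes the study education, physiotherapy and robot contact, and interpret the change with caution.
- Further covariates are optional and only possible if collected. The article mentions only demographic data and does not list the items, so age or education should not be assumed available.

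The cost is a change of wording in the analysis section, with no new data and no extra patients. The lower patient numbers under ANCOVA are no reason to recruit fewer than 90, because the correlation is unknown.
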